### Participants and Settings

The samples will comprise 152 participants of the cohort study of the Center for Aging Research (CSR) of the UNIFESP. The CSR is responsible for the EPIDOSO (“Epidemiologia do Idoso”) study, which is a cohort of elderly population living in the community district Vila Clementino in the city of São Paulo, Brazil. The EPIDOSO is the first longitudinal study in Latin America that aimed to identify factors that would influence healthy aging in elderly residents of the community. Vila Clementino is a neighborhood with homogeneous population without great significance of migration into or out of the neighborhood and represented by majority middle class population.

### Cohort Wave

Between December 2007 and April 2008, the CSR draws a random sample of 2,000 people 60 years or older living in a middle-class neighborhood, with high educational level and low migration rates, in the city of São Paulo, for a multicentric household survey to investigate the validity of the ADLs to assess need for help (46). After the home interview, all interviewees were invited to participate in an open cohort. A total of 1,155 elderly attended the invitation at that time and had a comprehensive geriatric and gerontological evaluation at the CSR of the university, which provided data on sociodemographic characteristics, referred chronic diseases, medications in use, cognitive status, and independence in daily life.

### Participants' Enrollment

Between June 2018 and May 2019, we contacted the participants of this cohort by phone calls, and they were invited to participate in the present study. We booked those who agreed for a new application of the comprehensive geriatric and gerontological evaluation, now including the Clinical Dementia Rating (CDR) scale (47, 48) applied by a trained professional through an unstructured interview with a relative of the participant. This enabled the selection of individuals with normal cognition (CDR = 0) or mild cognitive impairment (CDR = 0.5) in the study.

The participants of the cognitive stimulation and mindfulness trial answered a specific protocol that included Montreal Cognitive Assessment (MoCA) and a questionnaire to find out what computing level they had and if they have already experienced other sorts of mediations practices on the last 6 months.

After signing the consent form, we randomly assigned study subjects to two comparative groups: intervention and control, with an allocation ratio 1:1, following the sequence of arrival in the study as shown in Figure 1.

### Eligibility

To be admitted in the study, participants will meet the following inclusion criteria: (a) men and women 60 years or older; (b) elderly classified as cognitively normal (CDR = 0) and/or with mild cognitive impairment (CDR = 0.5); (c) be literate; (d) not have an advanced computer level; and (e) have a good hearing to follow the practices.

Exclusion criteria are as follows: (a) participants performing contemplative practices such as yoga, tai-chi-chuan, vipassana, Zen Buddhism, mindfulness, and other meditative practices in the last 6 months; (b) patients with acute phase of depression evaluated by the Geriatric Depression Scale (GDS-15) (49–51); (c) patients with psychotic diagnosis; (d) who are taking drugs that cause cognitive impairment; (e) participants who score 1.0 or more at the CDR (47, 48, 52) applied during the recruitment by a trained gerontologist in order to diagnose cognitive impairment.

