Thus, the aim of this study is to evaluate the feasibility and preliminary efficacy of the MBHP program on quality of life (primary outcome) of older adults assisted in PC comparing to a cognitive stimulation active control group. Our main hypothesis is that the MBHP is feasible and efficacious in promoting quality of life in people older than 60 years, and it will improve psychological health, self-compassion level, sleep quality, religiosity, and score at ADLs and prevent or delay cognitive decline in the elderly (secondary outcomes). Also, we hypothesize that the MBHP is superior to a cognitive stimulation group to promote those benefits.

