Randomization will be implemented using the Microsoft Excel. Each participant will be randomized individually for each of the two groups. The couples will be stratified into the same groups as it was also considered that, if they were allocated to be separated, one could teach another what was taught and then contaminate the sample. All randomization procedures will be made by a statistical professional who will only receive the identification number of the participants and will not interact with them at any time before, during, or after the intervention.

After the randomization, the participants will be invited to attend the CSR for a lecture, which we will inform which group they were randomized to and when the intervention will start. At this moment, we will hand the participants the informed consent in written form to be signed by the interested and the measure scales that were not filled during the screening such as Mindful Attention Awareness Scale (MAAS) (65, 66), Self-Compassion Scale (SCS) (67, 68), Depression Anxiety and Stress Scale (DASS-21) (69, 70), Pittsburg Sleep Quality Index (PSQI) (71, 72), and Duke Religious Index (Durel) (73, 74).

Due to the nature of the intervention, this will be a single-blind study, in which the outcomes assessment and analyses will be blind, but the participants will be aware of their group assignment.

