### Statistical Analysis

All analyses will be conducted using intention-to-treat and per-protocol analyses following the CONSORT recommendations for reporting the results (44).

Categorical variables will be described by absolute and relative frequencies. Numerical variables will be checked for their distributions through histograms and boxplots. If considered as having normal distribution, they will be described by mean and standard deviation. Otherwise, they will be described by medians and quartiles.

The primary outcome of this study is the quality of life measured by the WHOQOL-BREF and WHOQOL-OLD, and the secondary outcomes are cognitive function measured by the MoCA, level of consciousness at present measured by the MAAS, self-compassion measured by the SCS, Psychological Health measure by DASS-21, sleep quality measured by PSQI, and religiosity assessed by the Duke University Religion Index. Sociodemographic questions (sex, age, schooling), treatment group, and time will be the independent variables.

To verify the homogeneity between the study groups regarding sociodemographic measures at the initial time of the study, the groups will be compared by means of hypothesis tests of the type: χ^2^ and/or Fisher exact for categorical variables and multivariate analysis of variance (MANOVA) and/or Kruskal–Wallis for numerical or ordinal variables. A descriptive analysis of the sociodemographic categories regarding the sex, age, and schooling of both groups will be carried out.

Measures of preintervention (T0), post-intervention (T1), and follow-up (T2) outcomes may be compared by means of MANOVA for repeated measures. If necessary, Student *t*-tests will be conducted for paired or Wilcoxon data by applying corrections by the Holm or Bonferroni method. A Pearson correlation coefficient analysis will also be performed between the means of the primary outcomes and those of the secondary outcomes to examine the degree of changes in the outcome measures over time.

The difference between the measures T0 to T1, T1 to T2, and T0 to T2 can be compared between the intervention groups in MANOVA of repeated measures by means of Mann-Whitney tests. If necessary, these models will also be adjusted to assess the effects of time and intervention group, controlling for possible moderating variables.

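### CDR class (0 or 0.5) is known before randomization but is missing from the named covariates and the baseline check, at a modest cost in precision on the secondary cognitive outcome

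*Protocol article*

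**What the plan says.** **Who is admitted.** The Eligibility section takes participants "elderly classified as cognitively normal (CDR = 0) and/or with mild cognitive impairment (CDR = 0.5"). Under Recruitment, Procedures, and Randomization, a trained gerontologist rates the CDR with the help of an informant before anyone is allocated. Table 2 lists CDR at baseline only.

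**How they are allocated.** Participants' Enrollment describes two groups, "intervention and control, with an allocation ratio 1:1, following the sequence of arrival in the study". The randomization section adds "Each participant will be randomized individually for each of the two groups". The only use of stratification concerns spouses: "The couples will be stratified into the same groups". No CDR stratum is described.

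**What is claimed.** The Introduction hypothesises that the program will "prevent or delay cognitive decline in the elderly (secondary outcomes"). The secondary outcomes in the Statistical Analysis section include "cognitive function measured by the MoCA", recorded at baseline, post-intervention and 1 year. ADL appears in the hypothesis and in Table 2.

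**How it is analysed.** The Statistical Analysis section says "Sociodemographic questions (sex, age, schooling), treatment group, and time will be the independent variables". Its homogeneity check is confined to sociodemographic measures. Outcomes are compared as repeated measures, or as differences between time points with Mann-Whitney tests. A last clause reads "If necessary, these models will also be adjusted to assess the effects of time and intervention group, controlling for possible moderating variables".

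**The concern.** The eligibility criteria create two classes that the protocol itself labels differently, normal cognition and mild cognitive impairment. The class is plausibly prognostic for cognitive change over the roughly 16 months from baseline to follow-up (16 weeks plus 1 year). It is obtained for every participant through an informant interview, yet in the text shown it serves only as an entry gate.

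Two things are at stake, both on the cognitive outcomes. First, variation between the classes in rate of change stays in the error term. Second, if the one allocation actually drawn is uneven in CDR class, the stated baseline check would not show it and the stated covariate list would not correct for it. The adjustment clause names neither a variable nor a trigger, so the choice to adjust for CDR could be made after the data are seen.

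**Working it through.** **Inputs from the article.** 64 per group needed, 15% loss, 76 per group randomized, power 0.80, α 0.05 (Sample Size and Power Calculations).

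**Inputs assumed, because the article does not give them.** CDR 0.5 share p; shift g in MoCA change between the classes, in residual SD units, 0.3 to 0.8; detectable effect 0.5 SD.

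**1. The plan's own figure.** No effect size is stated. With d = 0.5, a two-sided t-test at α 0.05 and power 0.80 needs 63.77, so 64 per group. 64/0.85 = 75.3, so 76 per group and 152 in total. The stated figures are reproduced, and including CDR does not change them.

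**2. How uneven CDR can be by chance.** The SD of the difference in share between arms is √(2p(1−p)/76).

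| p | SD | 95% range (±1.96 SD) |
|---|---|---|
| 0.3 | √(0.42/76) = 0.074 | ±14.6 points |
| 0.4 | √(0.48/76) = 0.079 | ±15.6 points |
| 0.5 | √(0.50/76) = 0.081 | ±15.9 points |

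By the hypergeometric distribution with 76 per arm, a difference of 15 points or more has probability 5.1%, 4.7% and 7.4% at these three shares. At a share of 10% it is 0.1%.

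**3. What that does to the MoCA comparison.** The planned comparison is of change, so only a class difference in change matters. With 64 per arm, the 95% range of the shift due to imbalance is 1.96 × g × √(2p(1−p)/64).
- Smallest case, g = 0.3 and p = 0.2: 1.96 × 0.3 × 0.0707 = 0.04 SD.
- Largest case, g = 0.8 and p = 0.5: 1.96 × 0.8 × 0.0884 = 0.14 SD.

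**4. Error rate and power.** Simulation with 4,000 runs per scenario, 64 per arm, p of 0.2, 0.3 and 0.5:
- Unadjusted type I error is 0.043 to 0.052; adjusted it is 0.046 to 0.057. The mean unadjusted estimate under no effect lies within 0.006 SD of zero.
- Given a realized 15-point imbalance, with noncentrality 0.15g/√(2/64), the unadjusted type I error is 0.057 (g = 0.3), 0.071 (g = 0.5) or 0.104 (g = 0.8).
- Power at a true effect of 0.5 SD:

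| g | Unadjusted | Adjusted for CDR | Gain |
|---|---|---|---|
| 0.3 | 0.785–0.807 | 0.794–0.808 | 0.1 to 0.9 points |
| 0.5 | 0.769–0.786 | 0.785–0.801 | 1.5 to 2.2 points |
| 0.8 | 0.736–0.757 | 0.794–0.798 | 3.7 to 5.8 points |

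A direct calculation agrees. Leaving CDR out multiplies the residual variance by 1 + g²p(1−p). At g = 0.8 and p = 0.5 this is 1.16, the standardized effect falls to 0.5/√1.16 = 0.464, and power is 0.741 against 0.798 with adjustment.

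**5. Quality of life.** With an assumed class difference of 0.3 SD and p = 0.4, CDR explains 0.0216/1.0216, about 2% of the variance.

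These calculations ignore couples and class groups, which are a separate matter.

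**The case against.** A reader might infer that unstratified allocation lets CDR confound the claim about cognitive decline. The documents do not support that. Chance imbalance under randomization is random error, already covered by the standard error and α, and the simulated type I error is nominal. The higher conditional rates apply only once a large imbalance has occurred, which is uncommon.

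A reader might also take the difference in MoCA level between the classes as the measure of harm. With a 1 SD difference in level, a 15-point imbalance would shift the contrast by 0.15 SD, and at a 40% share CDR would explain 19% of the variance. But both the sample size section and the analysis section compare change from an earlier measurement, and a stable difference in level cancels there. What does not cancel is a difference in the rate of change, so this objection reduces the size of the point without removing it.

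Adjustment is not ruled out: the article allows it for possible moderating variables. That stands, but no variable or trigger is named, and a Mann-Whitney test of differences takes no covariate.

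Finally, this is a condensed article, and covariate detail may sit in a full protocol or analysis plan not shown. For that reason, silence about blocks or list generation is no finding. The point rests on what the article does state: a covariate list, and a baseline check limited to sociodemographic measures. Named age and schooling may also absorb part of what CDR would explain.

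**Conclusion.** The point holds as a minor, nearly free improvement and is no threat to validity. Leaving CDR out of the stated covariates and baseline check does not bias the treatment comparison or inflate its average type I error. It gives up from almost nothing to about 5 or 6 points of power on a secondary outcome, and it leaves the decision to adjust open until after the data are seen. The size rests on three assumptions: the CDR 0.5 share, a class effect on MoCA change of 0.3 to 0.8 SD, and a detectable effect of 0.5 SD. The primary outcome and the sample size are essentially untouched.

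**What to change.** In the Statistical Analysis section:
- Prespecify baseline CDR class (0 versus 0.5) as a covariate in the models for MoCA and ADL.
- Base the between-arm comparison of those outcomes on a model that accepts covariates, in place of a Mann-Whitney test of differences.
- Show CDR class by arm in the baseline table.

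Stratify the allocation list by CDR only if randomization has not yet taken place. Participants' Enrollment describes assignment in the past tense while the randomization section uses the future, so this step is probably no longer available. The analysis change is useful either way.

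The cost is one covariate in the models and one row in a table. CDR is already collected for everyone, so no new data are needed and the sample size stays as it is.

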### Instructors

Four mindfulness tutors will lead the MBHP groups—on Mondays, Tuesdays, Wednesdays, and Thursdays, respectively. All of them were already certified by the Mente Aberta – Brazilian Center for Mindfulness and Health Promotion and have at least 2 years of experience leading the MBHP protocol at the time of the study. The Mente Aberta certifying professional training follows the British and Brazilian guidelines for good practices of mindfulness (53). The cognitive stimulation control group will be conducted by an experienced gerontologist of the CSR who had a specific training in the protocol (described in detail below).

### The MBHP Protocol

The intervention in the MBHP-Elderly Study will be the MBHP program [(39); Table 1]. It was developed by Mente Aberta Center. It is originally an 8-session (2 or 1.5 h each) program based on the MBSR model created by Kabat-Zinn et al. (11). The MBHP is adapted to the context of PC with a framework that supports the learning process to individuals from different cultures and education backgrounds (54). It emphasizes exercises to be carried out at home or work environment in order to incorporate mindfulness into their daily lives through formal practices such as meditations and informal practices such as walking, eating, and talking with awareness. It also emphasizes the concepts of radical acceptance, values clarification, and positive psychology (54).

**Table 1 T1:** Mindfulness-Based Health Promotion (MBHP) program.

**Session**	**Practices**	**Homework**
1. Leaving the automatic pilot	Raisin exercise—body scan	Body-scan-mindful eating−9 dots exercise
2. Mindfulness in the body	Body scan—primary and secondary suffering—exploring breath—mindful breathing	Body scan-mindfulness in breathing-awareness of pleasant events (diary)—attention for routine activity and habit changing
3. Mindfulness in movement	Mindfulness in breath—hello, thank you, goodbye—mindful walking	Mindful breathing—mindful walking-awareness of unpleasant events (diary)—attention for routine walking
4. Expanding mindfulness	Mindful movements—mindfulness of sounds and thoughts−3 min practice	Sounds and thoughts practices−3 min practices—awareness of communication difficulties (diary)
5. Dealing with difficulties	Sounds and thoughts practice−3 min breathings space in doubles	Sitting meditation—body scan—movement practice—sound and thoughts practice−3 min practice at a challenge situation
6. Mindfulness and silence	Body scan—mindful breathing—mindful walking—mindful movements	Practice of choice—mindful conversation
7. Compassion	Sound and thoughts practice—sitting meditation—loving-kindness (for oneself and other)	Practice of choice—compassion practice
8. Mindfulness for life	Self-compassion practice—connection with values	Daily life mindfulness incorporation

The main techniques used in this program are “mindfulness in breathing,” “body scan,” “mindful walking,” “mindful movements,” and “3 min of mindfulness” (adapted from the program of the Breathworks Institute, UK). It also introduced the concepts of “first and second suffering” and the “Hi-Thanks-Bye” as psychoeducation techniques. The compassion and self-compassion practices are also included in the protocol, which might be useful for older people dealing with the self-criticism and low levels of acceptance of body changes. There is no consensus about potential unwanted effects of MBIs in the literature yet (55).

In this study, the MBHP sessions will be adapted and abbreviated for 1 h and a half per week for 8 weeks. After the 8-week protocol, four 1-h maintenance sessions will be performed every 15 days to match a 4-month intervention time period in full. We chose this format and length to be able to compare with the active control group (as described below). Moreover, studies that applied MBIs for longer months with older adults have been previously reported and may be beneficial to them (56, 57), as well as meeting lasting 1 h and 30 min instead of 2 h during the 8-week program (29, 30).

### Cognitive Stimulation Protocol

The active control group will receive a cognitive stimulation training in the CSR facility. This training is a computer class workshop based on a model proposed by Xavier et al. (58), which uses the staging methodology considering cognitive and functional resources accordingly to the level of complexity and difficulties from the executive functions theory. The basic workshop is considered a cognitive stimulation, and the participants will receive a class 1 h and 30 min once a week for 16 weeks (4 months).

The abilities learned at the workshop will be basic computer functions from development of the psychomotricity involving using mouse, keyboard, MS Paint, photo gallery, and PowerPoint presentations; surfing on the internet; and learning how to play online games and use social networks. The activities of the workshop are elaborated and adapted accordingly to the development of each class by the participants so that they get the same group level.

### Recruitment, Procedures, and Randomization

Overall, 152 elderly were recruited from the cohort of the CSR of the Universidade Federal de São Paulo from June 2018 to May 2019. Recruitment was conducted by invitation phone calls to the cohort list. Participants who showed interest in the research were scheduled to visit the center so that one of five researcher assistants would apply a comprehensive geriatric and gerontological evaluation named as Wide Geriatric and Gerontologic Assessment (WGGA), which comprise sociodemographic data and other measures' information needed for the recruitment such as GDS-15 (49–51) and baseline data such as quality of life [World Health Organization Quality of Life (WHOQOL) BREF and WHOQOL-OLD] (59–62) and ADLs, and then the MoCA (63, 64) is applied in order to evaluate cognitive function.

After this first step, a trained gerontologist applies the CDR (47, 48, 52) to evaluate if the participant has dementia or any cognitive impairment. The CDR evaluation requires a caregiver or a relative close to the older adult to be interviewed to inform about his cognition and behaviors (48). The participants who score 0 or 0.5 were included in the study.

After the screening and recruitment, the 152 participants approved in the inclusion criteria will be randomized and allocated into the groups. Married participants who meet the inclusion criteria will be allocated to the same groups; it was decided to do that because some couples need the support from one another to go to the center. The MBHP program group will then be randomized again into other four subgroups (19 participants each) because the MBI group is better availed when smaller. All the groups will follow the same assessment of the research, and the MBHP protocol will be led by instructors certified by Mente Aberta the whole time. The control group will also be randomized and allocated into small groups according to the number of computers in the computer lab (19 participants each).

Randomization will be implemented using the Microsoft Excel. Each participant will be randomized individually for each of the two groups. The couples will be stratified into the same groups as it was also considered that, if they were allocated to be separated, one could teach another what was taught and then contaminate the sample. All randomization procedures will be made by a statistical professional who will only receive the identification number of the participants and will not interact with them at any time before, during, or after the intervention.

After the randomization, the participants will be invited to attend the CSR for a lecture, which we will inform which group they were randomized to and when the intervention will start. At this moment, we will hand the participants the informed consent in written form to be signed by the interested and the measure scales that were not filled during the screening such as Mindful Attention Awareness Scale (MAAS) (65, 66), Self-Compassion Scale (SCS) (67, 68), Depression Anxiety and Stress Scale (DASS-21) (69, 70), Pittsburg Sleep Quality Index (PSQI) (71, 72), and Duke Religious Index (Durel) (73, 74).

Due to the nature of the intervention, this will be a single-blind study, in which the outcomes assessment and analyses will be blind, but the participants will be aware of their group assignment.

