### Assessment and Outcomes

The first two assessment points (baseline, post-intervention) will occur over a week before the intervention and on the last meeting of the maintenance group, and the follow-up will occur 1 year after the last meeting of the intervention. For the baseline, the sociodemographic questionnaire, WHOQOL-BREF, WHOQOL-OLD, MoCA, and ADL questionnaire occurred during the recruitment; all the other scales will be applied a week before the intervention starts. The measures of the intervention group will be on sheets of paper as most of the participants are not familiar with using electronic devices. The typing of the data will be made by two people to supervise and to guarantee no typing mistake of the collected data. SurveyMonkey software will be used for data collection for control group as the participants will learn how to use it on the cognitive stimulation classes. All the instruments have been validated into Portuguese with reliable psychometric properties and are available in Supplementary Files (48, 49, 60, 61, 63, 65, 68, 70, 71, 73).

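### Consent is placed both before and after randomization, and five secondary-outcome baselines are handed out at the session where participants learn their arm, which exposes those contrasts to bias

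*Protocol article*

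**What the plan says.** **Consent.** Participants' Enrollment puts consent first: "After signing the consent form, we randomly assigned study subjects to two comparative groups". Recruitment, Procedures, and Randomization puts it later. After randomization, participants come to a lecture at "which we will inform which group they were randomized to and when the intervention will start". The next sentence reads: "At this moment, we will hand the participants the informed consent in written form to be signed by the interested and the measure scales". Ethical Considerations and the Ethics Statement mention written consent but do not say when it is taken.

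**Scales.** The forms handed out at that lecture are those not completed at screening, named as MAAS, SCS, DASS-21, PSQI and DUREL. Assessment and Outcomes is compatible with this. It places the sociodemographic questionnaire, WHOQOL-BREF, WHOQOL-OLD, MoCA and ADL during recruitment, and says "all the other scales will be applied a week before the intervention starts". Table 2 marks all five later scales as T0 baseline.

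**Analysis.** Statistical Analysis states that "the secondary outcomes are cognitive function measured by the MoCA, level of consciousness at present measured by the MAAS, self-compassion measured by the SCS", and then adds DASS-21, PSQI and the Duke index, six in all. It plans repeated-measures comparisons over T0, T1 and T2 and between-arm comparisons of the T0-to-T1, T1-to-T2 and T0-to-T2 differences, by intention-to-treat and per protocol. Participants are not blinded.

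**The concern.** Two matters follow from the order of events at one session.

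First, a measure taken after the arm is known is a post-randomization measure, even if it is labelled baseline. Someone just told that they will train in mindfulness, or that they will attend computer classes, then rates their own mindfulness, self-compassion and distress. Any difference between arms that this creates at T0 goes straight into a change score and partly into a baseline-adjusted effect. Blinded outcome assessment gives no protection, because these are questionnaires answered by the participants.

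Second, if consent is signed only after the arm is announced, people can decline because of the arm they drew. If those who decline are then left out, the groups analysed are no longer the groups randomized. This second route reaches the primary outcome as well.

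**Working it through.** **1. Order of events, by section**

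| Event | Participants' Enrollment | Recruitment, Procedures, and Randomization | Assessment and Outcomes |
|---|---|---|---|
| Written consent | before randomization | after randomization, at the disclosure lecture | not stated |
| WHOQOL-BREF, WHOQOL-OLD, MoCA, ADL baseline | MoCA mentioned before assignment | at screening, before randomization | during recruitment |
| MAAS, SCS, DASS-21, PSQI, DUREL baseline | not stated | at the disclosure lecture | a week before the intervention |

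The conflict is in the first row only. On the five scales the sections agree with one another; the difficulty there is the design they describe.

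**2. Count of outcomes affected**

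Statistical Analysis lists MoCA, MAAS, SCS, DASS-21, PSQI and DUREL. All but MoCA have their baseline at the lecture: 5 of 6. The aims at the end of the Introduction also name ADLs as secondary; counting ADL makes it 5 of 7. The five are self-reported, except for five third-party items in the PSQI.

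**3. Size of the bias (illustration; s and r are assumed)**

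Let knowledge of the arm shift the T0 mean of one arm relative to the other by s SD. Assume that the shift is transient (absent at T1 and T2), that SDs are equal over time, and that baseline and follow-up correlate at r.

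- Change score: absolute bias = s
- Baseline-adjusted score: the within-arm slope is r, so absolute bias = r × s

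The sign is opposite to that of the shift. To see the effect on a test, take the plan's minimum of 64 per arm. The standard errors in SD units are √(2(1−r)) × √(2/64) for the change score and √(1−r²) × √(2/64) for the adjusted score. The two-sided 5% test then rejects a true null as follows:

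| s | r | change: bias | change: type I error | adjusted: bias | adjusted: type I error |
|---|---|---|---|---|---|
| 0.1 | 0.5 | 0.10 | 8.7% | 0.05 | 6.2% |
| 0.2 | 0.5 | 0.20 | 20.5% | 0.10 | 10.0% |
| 0.3 | 0.5 | 0.30 | 39.6% | 0.15 | 16.5% |
| 0.1 | 0.7 | 0.10 | 11.3% | 0.07 | 8.6% |
| 0.2 | 0.7 | 0.20 | 30.9% | 0.14 | 19.8% |
| 0.3 | 0.7 | 0.30 | 59.1% | 0.21 | 38.4% |

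**4. Refusal after disclosure (illustration)**

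The plan's numbers reproduce if a standardized difference of 0.5 is assumed: a two-sided t-test at 0.05 with power 0.80 needs 63.8, so 64 per arm, and 64/0.85 = 75.3, so 76. The sample size section states no effect size, so 0.5 is an inference. If refusers are dropped on top of the 15% loss, the number left per arm is 76 × (1 − refusal) × 0.85:

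| Assumed refusal | Left per arm | Power at assumed 0.5 |
|---|---|---|
| 0% | 64.6 | 0.81 |
| 5% | 61.4 | 0.79 |
| 10% | 58.1 | 0.76 |
| 15% | 54.9 | 0.74 |

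The loss of power is modest. The larger risk is that refusal differs by arm.

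**The case against.** Much can be said for the plan, and several points stand.

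- **The primary baseline is clean.** WHOQOL-BREF and WHOQOL-OLD are taken at recruitment, as are MoCA and ADL. A reader might infer that the quality-of-life baseline is contaminated; the documents show that it is not. The T1-to-T2 contrast does not use T0 at all.
- **Bias is possible, not shown.** A reader might infer that the five baselines are biased. The documents give neither size nor direction. Both arms are active and the Discussion expects both to help, so disappointment in one arm is not self-evident. DASS-21 asks about the previous week and PSQI about the last month, mostly before disclosure, and DUREL covers habitual practice. Reporting can still shift, but there is no reason to expect one common shift on all five.
- **Intention-to-treat has not failed.** It would fail only if people refuse after disclosure and are then left out. The plan promises intention-to-treat and nowhere says that refusers are excluded.
- **No percentage of a design effect can be quoted.** It is tempting to compare the bias with a design difference of 0.5, but the protocol states none.
- **The enrolment section conflicts on consent only.** It says nothing about when the five scales are completed.
- **The forms might be collected before the announcement, within the same session.** The text does not say so; its order is announcement, then forms. Figure 1 is not available to check. The cohort-nested label does not help either, since no design with consent after randomization is described and the enrolment section states the reverse.

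These points limit the size and reach of the problem. They do not remove the contradiction on consent or the timing of the five scales.

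**Conclusion.** The concern holds in a limited form. The protocol gives two incompatible orders for consent and randomization, and they must be reconciled. As written, it also takes the T0 values of MAAS, SCS, DASS-21, PSQI and DUREL at the session where the arm is announced. This exposes to bias the T0-to-T1 and T0-to-T2 contrasts for five of the six secondary outcomes in the analysis section (five of seven with ADL).

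For an assumed transient shift of 0.1 to 0.3 SD, the bias is 0.1 to 0.3 SD on change scores and 0.05 to 0.15 SD after baseline adjustment at r = 0.5 (0.07 to 0.21 SD at r = 0.7). These figures rest entirely on the assumed shift and correlation. The primary outcome is reached only through selective refusal after disclosure, and only if refusers are left out of the analysis.

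**What to change.** **For anyone not yet enrolled:** obtain written consent before randomization, as the enrolment section states, and have all five scales completed and handed in before the arm is revealed. If the scales stay at the lecture, only the order within that session changes, and no extra visit is needed. Moving consent means taking it at the screening visit.

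**For those already enrolled**, probably the larger group: the recruitment section reports all 152 as recruited between June 2018 and May 2019, although Trial Status calls recruitment ongoing.

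- State the consent order that was actually followed and correct the section that is wrong.
- Report refusals after disclosure by arm.
- Keep everyone randomized in the intention-to-treat set, as far as their consent allows.
- Compare the five scales on T1 and T2 scores without the post-disclosure baseline, at least as a sensitivity analysis.

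The last step costs some precision. With unit variance, the post-score has variance 1 against 1 − 0.5² = 0.75 for a baseline-adjusted score at an assumed r = 0.5, which is one third more (1/0.75 = 1.33). Against a change score there is no loss at that correlation, since 2(1 − 0.5) = 1. At r = 0.7 the comparison is 1 against 0.51 (adjusted) and 0.60 (change).
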